MSCs is safe and well-tolerated in mild to moderate PD patients. The treatment effect likely relies on peripheral immune modulation. The study recruited 20 subjects with mild-moderate PD that were sequentially assigned to one of four doses: 1, 3, 6, or 10 X 10^6 MSCs/kg given IV and evaluated at 3, 12, 24, and 52 weeks post-infusion. Primary outcome safety measures were defined as the absence of immediate transfusion reaction, study-related adverse events, organ damage, or immunogenic reactions. Secondary outcomes were defined by the therapy's impact on peripheral markers, PD progression, and changes in brain perfusion.

All 20 patients received a single MSCs IV infusion. During the first 24 hrs post-infusion, three patients reported TEAEs, one with phlebitis, one with an antecubital fossa hematoma, and one with a headache (*Table 2*). The first patient had 3 cm superficial phlebitis Grade 2 Infusion-Related Allergic Reactions (NCI-CTCAE criteria) that required local medical management. The other two patients had mild symptoms and did not require any treatment. All patients left the research unit with full resolution of their symptoms. In subsequent follow-up, 50% of the patients reported TEAEs; most of them were mild, with dyskinesia (20%, N=4) and hypertension (20%, N=4) as the most common. Two of the patients experiencing dyskinesias required levodopa reduction for resolution and the remaining resolved without intervention. All hypertension cases were reported between 3 and 12 weeks after infusion and were followed by their primary care physicians. Of those, three cases were transient, and one patient was diagnosed with stage 2 hypertension and is currently under medical management.

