#### 5.1.2 Secondary outcomes

Assess 1) safety and tolerability; 2) secondary measurements of clinical efficacy and 3) explore putative mechanisms of action for the effect of MSC

1. MSC therapy will demonstrate safety and tolerability comparable to placebo in terms of serious adverse reactions and immunologic responses.

- New-onset organ failure defined as a significant acute change in the kidney or liver function, leukocytosis, leukopenia or anemia sustained over 3 months; > 75 % reduction in GFR compared to baseline; altered liver function as defined by ALT >150 U/L and or total bilirubin >1.6 mg/dl; or leukopenia defined as < 4K WBC count or anemia as defined by Hgb < 12 for men and < 11 for women.
  - Immunologic responses: Donor specific antibodies (DSA) in serum of patients will be measured and compared to baseline to determine if there is a development of antibody response to donor HLA. (Please refer to section 11.2)
2. MSC therapy will improve motor function, disability, quality of life, non-motor symptoms, cognition, and behavioral changes relative to placebo.
- Motor function: characterized by a change in MDS-UPDRS Total and Motor scores and Timed-Up-and-Go (TUG) from baseline. Immediate response will be assessed at weeks 29, 39, 52, and 78. Normal progression in UPDRS-T is defined by > 8-14 points per year Therefore abnormal clinical deterioration is an increase of >12 points per year in the “Off” state. For the UPDRS-M, the literature supports a natural progression of 3-6 points per year and this equivalent for the MDS-UPDRS motor section; therefore, abnormal clinical deterioration is an increase of > 6 points per year. TUG progression is defined as a +/- 3 seconds difference every 6 months.
  - Global measurement of disability as measured by the change in the screening “Off” modified Hoehn and Yahr (H&Y) at the final visit. Expected progression is defined as a < 1.0 increase in H&Y every 2 years. Therefore, clinically significant deterioration would be > 0.5 increase in the H&Y over 1-year.

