## 14.3 Statistical analysis

Hypothesis 1.1. At least one active MSC group will demonstrate improved scores ( $\geq -5$ ) relative to placebo at 62 weeks follow-up. Generalized linear modeling will evaluate the MDS-UPDRS motor section as a function of treatment. Application of the decision-rules, discussed in the Sample Size Section, to the resulting posteriors will identify the candidate doses that warrant further investigation.

Hypothesis 2.1. Generalized linear modeling will characterize serious adverse reactions, significant worsening of general and motor functional state, activities of daily living, and peripheral immunologic responses. In each case, the subtraction of the posterior distribution for the treatment condition from the posterior distribution of the placebo condition will permit estimates of the posterior probability that the active condition is better than or equal to the control.

Hypothesis 2.2. Generalized linear modeling will estimate the improvement in motor function, disability, quality of life, non-motor symptoms, cognitive and behavioral symptoms as a function of treatment.

Hypothesis 3.1. Bayesian, multilevel structural equation modeling will evaluate the degree to which cytokines, chemokines, growth factors, and neurotransmitters transmit the effect of treatment to the MDS-UPDRS motor section at 62 weeks.

Hypothesis 3.2. Separate multilevel generalized linear modeling to account for correlations due to repeated observations within participants will evaluate the MDS-UPDRS motor section as a function of time and time-varying covariates, including kinetic parameters of  $\alpha$ Syn-PMCA in plasma and CSF before and after treatment.

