#### 14.4 Interim analyses

At Week 29 will mirror those at trial completion, but only for those outcomes on which data has been collected at that point:

Hypothesis 1.1. At least one active MSC group will demonstrate improved scores ( $\geq -5$ ) relative to placebo at 40 weeks follow up. Generalized linear modeling will evaluate the motor MDS-UPDRS as a function of treatment.

Hypothesis 2.1. Generalized linear modeling will characterize severe adverse reactions, significant worsening of general and motor functional state, activities of daily living, and peripheral immunologic responses. In each case, the subtraction of the posterior distribution for the treatment condition from the posterior distribution of the placebo condition will permit estimates of the posterior probability that the active condition is better than or equal to the control.

Hypothesis 2.2. Generalized linear modeling will estimate the improvement in motor function, disability, quality of life, non-motor symptoms, cognitive and behavioral symptoms as a function of treatment.

Hypothesis 3.1. Bayesian, multilevel structural equation modeling will evaluate the degree to which cytokines, chemokines, growth factors, and neurotransmitters transmit the effect of treatment to the MDS-UPDRS at 40 weeks.

Hypothesis 3.2. Separate multilevel generalized linear modeling to account for correlations due to repeated observations within participants will evaluate MDS-UPDRS Motor as a function of time and time-varying covariates, including kinetic parameters of  $\alpha$ Syn-PMCA in plasma and CSF before and after treatment.

While multiple analyses often require correction for Type I Error, the Bayesian approach to analysis, because it obeys the likelihood principle, does not require this. Moreover, given the

degree of uncertainty that will exist in the form of the posterior distribution variances, the primary concern will be with bringing the trial to a premature conclusion for lack of benefit, when in fact, such benefit does exist (Type II Error).

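### The tolerability claim rests on serious adverse reactions as its only adverse-event variable, and the interim analysis replaces these with severe reactions

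*Protocol*

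**What the plan says.** The second objective in Protocol 5.1.2 reads: "MSC therapy will demonstrate safety and tolerability comparable to placebo in terms of serious adverse reactions and immunologic responses". Its laboratory part covers kidney and liver function and blood counts, ending "or leukopenia defined as < 4K WBC count or anemia as defined by Hgb < 12 for men and < 11 for women", and the count changes are described as sustained over 3 months.

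Hypothesis 2.1 in 14.3 gives the model: "Generalized linear modeling will characterize serious adverse reactions, significant worsening of general and motor functional state, activities of daily living, and peripheral immunologic responses". Subtracting the posteriors by arm "will permit estimates of the posterior probability that the active condition is better than or equal to the control". No threshold or margin for comparable is stated.

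Section 14.4 says the interim analyses mirror the final ones, but its Hypothesis 2.1 opens: "Generalized linear modeling will characterize severe adverse reactions". The rest of that sentence matches 14.3. Section 12.4 lists the CTCAE severity grade (item 1) and whether the event is serious (item 7) as two separate assessments of every adverse event.

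On Phase I, section 3.5 says of the events at follow-up: "most of them were mild, with dyskinesia (20%, N=4) and hypertension (20%, N=4) as the most common".

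**The concern.** Tolerability is usually shown by common, non-serious events. The protocol makes a tolerability claim against placebo but admits only serious events to the modelled adverse-event comparison. In a trial of 45 patients that class may be nearly empty, while the events Phase I recorded most often would rarely qualify for it.

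Two things are at stake. The primary objective is to select the safest as well as the most effective number of infusions, so the safety comparison should be able to carry information. And if the event class differs between interim and final, the two safety results do not describe the same quantity and cannot be read as a sequence.

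**Working it through.** **No safety figure to reproduce.** The 72% in 14.2 belongs to Hypothesis 1.1 (motor score). The protocol gives no operating characteristic for Hypothesis 2.1.

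**Inputs from the protocol.** 15 patients per arm (6.5). Phase I counts across groups A to D, 5 patients each (table in 3.5):
- dyskinesia 1+0+2+1 = 4/20, the only event rated probably related; two patients needed levodopa reduction
- low lymphocytes 3+2+0+1 = 6/20, rated possibly related, footnoted as mild and transient
- hypertension 2+2+0+0 = 4/20, rated unlikely related

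**Assumptions.** The true serious-event rate is 2% to 5%. Event rates have a Jeffreys prior, so the posterior is Beta(x + 0.5, n − x + 0.5). The protocol states neither.

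**Step 1: how often the serious-event comparison is empty.** P(no event in an arm) = (1 − rate)^15.
- at 2%: 0.98^15 = 0.74
- at 5%: 0.95^15 = 0.46

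If both arms share the rate, both are empty with probability 0.98^30 = 0.55 or 0.95^30 = 0.21.

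**Step 2: what an empty comparison returns.** With 0/15 v 0/15 the two posteriors are identical, so P(MSC worse) = 0.50. A uniform prior gives the same. The one-sided 95% upper bound on a rate after 0/15 is 1 − 0.05^(1/15) = 18%.

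**Step 3: what a non-serious event could return.** If dyskinesia recurs at 20%, an arm of 15 shows at least one case with probability 1 − 0.8^15 = 96%, and 30 × 0.2 = 6 cases are expected on MSC. P(MSC worse) then depends on the placebo count:

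| MSC v placebo | P(MSC worse) |
|---|---|
| 6/30 v 0/15 | 0.98 |
| 6/30 v 1/15 | 0.88 |
| 6/30 v 2/15 | 0.70 |
| 6/30 v 3/15 | 0.49 |
| 3/15 v 1/15 (one MSC arm) | 0.86 |
| 3/15 v 2/15 (one MSC arm) | 0.69 |

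For 3 against 2 infusions, 4/15 v 3/15 gives 0.67 that 3 infusions is worse.

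**Step 4: whether the other modelled variables fill the gap.**
- Motor worsening: after screening the schedule in section 10 has the MDS-UPDRS OFF only, a poor setting for an event that two Phase I patients resolved by reducing levodopa.
- MDS-UPDRS Part IV (motor complications) enters only as part of the total score.
- The blood criterion uses total white cells below 4K, sustained. A transient fall in lymphocytes need not meet it.
- ADL and immunologic responses measure something else.

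Capture is therefore indirect.

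**Step 5: interim against final.** The two Hypothesis 2.1 sentences differ only in severe versus serious. Because 12.4 grades these separately, the interim does not mirror the final on this variable.

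**The case against.** The strongest reply is that adverse events of every grade are collected and graded (12.4), the DSMB reviews aggregate data after each infusion (section 16), and tables of adverse events by arm normally belong in the statistical analysis plan, which is not shown. That stands as far as it goes: the absence of such tables from the protocol is no finding. What remains is what the protocol itself fixes, namely the event class attached to the claim in 5.1.2 and 14.3, and the changed word in 14.4.

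It can also be said that Hypothesis 2.1 models more than serious reactions, and that item e of the serious-event definition in 12.2 could bring in an excess of mild events. The first is correct, and Step 4 allows for it. The second helps little, since item e states no expected rate and cannot classify a single case.

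Sparse serious events are a limit of any trial this small, and the added contrasts are not decisive either: with 2 or 3 placebo cases the dyskinesia comparison falls to 0.70 or 0.49. Both remarks stand and limit what the fix can deliver.

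A reader might infer four stronger statements that the documents do not support:
- *That these harms are dose-related.* No Phase I count rises steadily from group A to D, and Phase I was single-dose and uncontrolled.
- *That hypertension is a shown harm of MSC.* It was rated unlikely related and did not occur in groups C and D; of the four, "three cases were transient, and one patient was diagnosed with stage 2 hypertension".
- *That reactions means only events the investigator attributes to treatment.* The Phase I table heads its whole event column as adverse reactions, including an event rated unlikely related, and 12.2 defines serious without causality.
- *That comparability can be concluded with none of these events tested.* No rule for concluding it exists, a posterior of 0.50 would not support it, and some events are reached indirectly.

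**Conclusion.** The point holds in a limited form. The protocol's claim of comparable tolerability has serious adverse reactions as its only adverse-event variable, and the interim uses a different class although it is described as a mirror. Under an assumed serious-event rate of 2% to 5%, an arm of 15 is empty with probability 74% to 46%, and a comparison of two empty arms returns 0.50. Most Phase I events would fall outside the class and reach the model only indirectly.

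A comparison of all graded events would be more informative but not definitive. Its value rests on the placebo background rate, which the protocol does not give, on a prior that had to be assumed, and on Phase I rates from 20 patients. At the dose used here, if groups A to D follow the dose order in 3.5, dyskinesia and low lymphocytes were each seen in 1 of 5. This is a change worth making, and it does not show that the safety objective fails.

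**What to change.** In 5.1.2 and in Hypothesis 2.1 of both 14.3 and 14.4:

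1. Apply the same posterior comparison by arm to all treatment-emergent adverse events, stated to be regardless of attribution, with serious events and CTCAE grade 3 or higher as named subsets.
2. Prespecify dyskinesia (adverse-event reports and MDS-UPDRS Part IV) and lymphocyte count (CBC differential) as events of interest.
3. Reconcile serious and severe, and use one event class at interim and final.

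The cost is wording and a few more models on data already collected, with no new procedures. The downside is a few more safety contrasts, which should be labelled descriptive.

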#### 14.4 Interim analyses

At Week 29 will mirror those at trial completion, but only for those outcomes on which data has been collected at that point:

Hypothesis 1.1. At least one active MSC group will demonstrate improved scores ( $\geq -5$ ) relative to placebo at 40 weeks follow up. Generalized linear modeling will evaluate the motor MDS-UPDRS as a function of treatment.

Hypothesis 2.1. Generalized linear modeling will characterize severe adverse reactions, significant worsening of general and motor functional state, activities of daily living, and peripheral immunologic responses. In each case, the subtraction of the posterior distribution for the treatment condition from the posterior distribution of the placebo condition will permit estimates of the posterior probability that the active condition is better than or equal to the control.

Hypothesis 2.2. Generalized linear modeling will estimate the improvement in motor function, disability, quality of life, non-motor symptoms, cognitive and behavioral symptoms as a function of treatment.

Hypothesis 3.1. Bayesian, multilevel structural equation modeling will evaluate the degree to which cytokines, chemokines, growth factors, and neurotransmitters transmit the effect of treatment to the MDS-UPDRS at 40 weeks.

Hypothesis 3.2. Separate multilevel generalized linear modeling to account for correlations due to repeated observations within participants will evaluate MDS-UPDRS Motor as a function of time and time-varying covariates, including kinetic parameters of  $\alpha$ Syn-PMCA in plasma and CSF before and after treatment.

While multiple analyses often require correction for Type I Error, the Bayesian approach to analysis, because it obeys the likelihood principle, does not require this. Moreover, given the

degree of uncertainty that will exist in the form of the posterior distribution variances, the primary concern will be with bringing the trial to a premature conclusion for lack of benefit, when in fact, such benefit does exist (Type II Error).

## **15. Data collection and management**

### **15.1 Records to Be Kept**

The master trial file will include but not be limited to source documents, monitoring visit logs, regulatory documents, investigator and coordinators CVs and appropriate certifications, and correspondence pertaining to the trial. Source data is defined as all information in original records of clinical findings, observations, copies or other activities occurring in a clinical trial. These source data are necessary for the data quality of the clinical trial.

### **15.2 Data Management**

The Principal investigator will complete an enrollment log to permit the identification of each subject and will file the master log in the study file. Additionally, the research coordinator will create a chart for each subject in which all CRF data will be recorded. The Chart will be protected with HIPAA compliant techniques. The research scientist will create a database in REDCap that meets all verification and validation requirements of FDA rule 21 CFR 11, including reference to all pertinent FDA-provided guidelines. The study will use a REDcap database to store the de-identified information of all the visits for each subject.

#### Source Data and Documentation

Source documentation will be available to confirm data collected in the CRF and for resolution of SAE/AEs. A photocopy of the Label (s) on the Cell bag must be retained in the Coordinators source document binder but the bag may be discarded per hospital standard for blood products. Additionally, a chart of copied progress notes, vital sign records, imaging and lab result from the observation period must be retained in the study documents to verify presence or absence of AEs. A common term for this chart is “Shadow Chart” since it shadows the actual patient chart. The Shadow Chart must be protected with the same HIPAA compliant techniques as actual charts are protected. Data from any subsequent admission need only be retained as it applies to AEs.

#### CAGT Documentation

Records are kept of all of the items that are cited. These include:

- Donor identity
- Donor infectious disease testing as indicated in the CMC section
- Risk behavior questionnaire
- Health evaluation for donation
- Former donor eligibility declaration
- Records of all cell culture procedures
- Results of all in-process and release tests as described in the CMC section

Cells are stored according to Standard Operating Procedures using a formal inventory system that includes the sample identity, date of cryopreservation, sample location, donor identification, and passage number.

#### Data Quality Assurance

The Study PI or designee will conduct ongoing subject data quality assurance audits. The audit may include, but will not be limited to, a review of all subject ICFs, a review of CRFs and source documents, a review of regulatory documents, an assessment of trial conduct, and compliance. Data quality will be maintained by establishing a written Data Management Plan describing all applicable aspects of the data management process including: Developing a database that meets all verification and validation requirements of FDA rule 21 CFR 11, including reference to all pertinent FDA-provided guidelines.

### **16. Data safety monitoring board (DSMB)**

An independent DSMB will monitor the conduct of the trial and subject safety based on the review of the aggregate data one-month post each infusion. The DSMB will review the aggregate data after each infusion of the initial 22 patients and determine the safety to proceed to the next infusion. The DSMB will review the aggregate data for all the patients in order to determine safety regarding neurological and physical status. At any review, the DSMB may recommend the study continues as per protocol or recommend changes to the protocol or the conduct of the study. The DSMB can recommend suspension or study termination at any time for any reason.

The DSMB Plan will be formulated and agreed upon by the Primary Investigator and DSMB Board. The DSMB will be notified within 24 hours of an SAE. All or the majority of the DSMB members will meet to discuss the SAE report promptly.

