## 10. Study schedule

The study will last a total of one year and 8 months (88 weeks) per patient (3 groups) and will include 11 clinical visits and 10 telephone evaluations (*Please see section 10.3 for the study timeline and 10.4 for study schedule*).

There are 6 types of clinical visits: Screening, Baseline, Infusion, Safety and Clinical assessment, unscheduled visit, and final visit plus phone call evaluations starting after the first infusion.

- Visit #1 Screening Visit (between week -12 to week -3): after signing the consent and discussing the purpose and timeline of the study, the PI will confirm the PD diagnosis and establish the current disease stage. At this visit, the CRU staff will collect blood for laboratory assessment. The purpose of this visit is to ensure that the patient meets the inclusion and exclusion criteria.
- Visit #2 Baseline visit (between week -11 to week-1): the purpose of this visit to obtain baseline measurements on serum, plasma, CSF, and neuroimaging.
- Visit #3 Infusion Day (week 0): First IV MSCs infusion.
- Visit #4 Clinical and Safety assessment (week 9+/-1.5 week): the purpose of this visit is to determine the safety and the immediate immunological, physical and neurological response to the first infusion.
- Visit #5 Infusion Day (week 18+/-1 week): Second IV MSCs infusion.
- Visit #6 Clinical and Safety assessment (week 27+/-1.5 week): the purpose of this visit is to monitor safety and the immunological, physical and neurological response to the second infusion.
- Visit #7 Infusion Day (week 36+/-1 week): Third IV MSC infusion
- Visit #8 Clinical and Safety assessment (week 40+/-1.5 week): the purpose of this visit is to monitor the safety and the immunological, physical and neurological response to the third infusion. Additionally, to collect enough data for our first interim analysis.

- Visit #9 Clinical and Safety assessment (week 49+/-1.5 week): the purpose of this visit is to monitor the safety and the immunological, physical, and neurological response to the infusions.
- Visit #10: Clinical and Safety assessment (week 62+/-1.5 week): the purpose of this visit is to monitor the safety and the immunological, physical, and neurological response to the infusions.
- Visit # 11: Final visit (week 88+/-1.5 week): the purpose of this visit is to determine the physical and neurological response to the complete MSC treatment.

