## 10.2 Telephone or email evaluations

These will occur at week 1, week 4, week 13, week 19, week 23, week 31, week 38, week 44, week 55, and week 75. In order to maintain continuous monitoring of the presence of AEs after the infusion visit, patients would either receive a phone call or an email to monitor signs or symptoms of adverse reactions to the transfusion, at regular intervals until the study end, with a total of 10 evaluation calls/emails (*See appendix O for a copy of the Telephone evaluation form*).

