|                     | MDS-UPDRS On                                                     | X                         |                            |                  |                           |                          |                            |                          |                               |                               |                            |                               |                            |                                   |
|                     | Questionnaires: ADL, PAS, GDS, PDQ-
39, C-SSRS, EQ-5D-5L, NMS | X                         |                            |                  | X                         |                          | X                          |                          | X                             |                               | X                          | X                             |                            | X                                 |
| Laboratory          | Lumbar puncture**                                                |                           | X                          |                  |                           |                          |                            |                          |                               | X                             |                            |                               |                            |                                   |
|                     | CBC with differential and CMP                                    | X                         |                            |                  | X                         |                          | X                          |                          | X                             |                               |                            | X                             |                            | X                                 |
|                     | Dipstick UA                                                      | X                         |                            |                  |                           |                          |                            |                          |                               |                               |                            | X                             |                            |                                   |

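### The DSMB's decision to proceed to infusions 2 and 3 is tied to one-month data, but after discharge the first examination, CBC/CMP, DSA and MDS-UPDRS come 7.5-10.5 weeks (infusion 1) or 6.5-11.5 weeks (infusion 2) later

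*Protocol*

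**What the plan says.** **DSMB (section 16).** The board monitors conduct and safety "based on the review of the aggregate data one-month post each infusion". For the early cohort it is to "review the aggregate data after each infusion of the initial 22 patients and determine the safety to proceed to the next infusion". It also reviews all patients' aggregate data "in order to determine safety regarding neurological and physical status". Details are left to a DSMB plan that is not shown.

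**Visits (section 10).** Infusions fall at week 0, week 18 ± 1 and week 36 ± 1. The first clinic visit after infusion 1 is "Visit #4 Clinical and Safety assessment (week 9+/-1.5 week"; the first after infusion 2 is "Visit #6 Clinical and Safety assessment (week 27+/-1.5 week". Visit 8 follows infusion 3 at week 40 ± 1.5. Section 10.2 lists the telephone or email contacts: "These will occur at week 1, week 4, week 13, week 19, week 23, week 31, week 38" and later; section 10 gives them a window of 7 days either way. Section 10.1.3 requires a full physical and neurological examination before discharge on each infusion day.

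**Laboratory tests.** The schedule table's row "CBC with differential and CMP" is marked at screening, Visits 4, 6, 8 and 11, and early termination. DSA is marked at baseline and at the same later visits. The blood lists in section 10.1.4 (Visits 4 to 10) and section 10.1.5 (final visit) name DSA, peripheral markers and alpha-synuclein, but no blood CBC or CMP. The only CBC in 10.1.4 is on cerebrospinal fluid. The screening list in 10.1.1 names both blood tests.

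**DSA hold.** Section 11.2 suspends a patient's infusions if DSA are found at week 8 or week 21. Section 10.1.4 has the preceding visit's DSA result reviewed at Visits 4 and 6 only.

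**The concern.** The new exposure in this trial is repeat dosing; the Phase I study gave one infusion. Section 3.5 places delayed antibody-mediated reactions within 3-4 weeks of an infusion, and section 11.2 warns that sensitisation could lead to antibody-mediated rejection at the following one. The Phase I adverse-event table lists decreased lymphocytes in 3 + 2 + 0 + 1 = 6 of 20 patients, mild and transient, rated possibly related. DSA and blood counts are the tests that would show such signals.

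If the decision to proceed is taken at one month, it comes before those tests. A DSA response, a liver or blood-count change, or motor worsening found at Visit 4 or 6 would then arrive after the board had judged it safe to proceed. The board would also have to judge neurological and physical status for patients not examined since leaving the unit on infusion day.

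**Working it through.** **1. From infusion to the first post-discharge assessment.** The inputs are the visit weeks and windows in section 10, counted from infusion 1 at week 0. Shortest gap = (visit week − its window) − (infusion week + its window); longest gap = (visit week + its window) − (infusion week − its window).

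| Interval | Shortest | Nominal | Longest |
|---|---|---|---|
| Infusion 1 to Visit 4 | 7.5 − 0 = 7.5 | 9 | 10.5 − 0 = 10.5 |
| Infusion 2 to Visit 6 | 25.5 − 19 = 6.5 | 9 | 28.5 − 17 = 11.5 |
| Infusion 3 to Visit 8 | 38.5 − 37 = 1.5 | 4 | 41.5 − 35 = 6.5 |

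Only infusion 3 has a clinic visit near one month, and no infusion follows it.

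**2. Against the one-month point.** One month is 365.25 / 12 / 7 = 4.35 weeks.
- Visit 4 comes 7.5 − 4.35 = 3.15 to 10.5 − 4.35 = 6.15 weeks after it.
- Visit 6 comes 6.5 − 4.35 = 2.15 to 11.5 − 4.35 = 7.15 weeks after it.

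**3. What a patient's own record holds at one month.** It holds infusion-day vital signs and the pre-discharge examination, the telephone or email checks, and any SAE report or unscheduled visit. The check nearest one month is at week 4 ± 1 after infusion 1 (3-5 weeks) and at week 23 ± 1 after infusion 2 (22 − 19 = 3 to 24 − 17 = 7 weeks). One month after infusion 2 the Visit 4 results exist too, but they predate infusion 2.

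**4. The DSA hold.**
- Week 8 lies inside Visit 4's window (7.5-10.5). Week 21 lies outside Visit 6's window (25.5-28.5), and no DSA is scheduled then.
- The DSA sample before Visit 4 is the baseline one, so the review at Visit 4 covers baseline.
- The review at Visit 6 covers the Visit 4 sample, after infusion 2 has been given.
- No listed review covers the Visit 6 sample before infusion 3. The infusion-visit list in 10.1.3 contains no DSA check.

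**5. Blood CBC/CMP.** The table marks it at four scheduled visits after the first infusion (4, 6, 8, 11). The lists for those visits name it at none.

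**6. Room to move the decision.** From the latest Visit 4 to the earliest infusion 2 is 17 − 10.5 = 6.5 weeks. From the latest Visit 6 to the earliest infusion 3 is 35 − 28.5 = 6.5 weeks. The nominal gap is 9 weeks in both cases.

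**The case against.** - **The gating sentence gives no month.** The one-month timing stands in the general monitoring sentence. A decision after Visit 4 or 6 would be compatible with the sentence about the first 22 patients, and the DSMB plan may say so. This stands as a matter of wording. But one month is the only review time the protocol states, and a plan that kept it would add no draws to the schedule.
- **One month has a rationale.** It matches the 3-4 week window for delayed reactions, and the calls track that window. This supports keeping a one-month adverse-event review. It does not supply laboratory or antibody data for a decision to proceed.
- **The data are aggregate.** When later patients reach one month, earlier patients' Visit 4 results may be available. True, but this does not help the first patients, and it cannot show whether a given patient is sensitised.
- **Other safeguards exist.** The DSMB may recommend stopping at any time and hears of SAEs within 24 hours. Motor worsening at 6 months triggers a mandatory review, and Visit 6 supplies scores before infusion 3. These are real protections. However, the triggers do not name DSA or laboratory change as such, and the 6-month motor trigger comes after infusion 2.
- **The DSA hold is the intended protection.** Section 8.6 draws DSA between infusions and moves sensitised patients to a modified schedule. Week 21 looks like a leftover, since Appendix E still places Visit 6 at week 20. The governing algorithm (11.2.1) is a figure not shown. The intent is clear; the stated week and review points do not deliver it.
- **CBC/CMP is in the table.** Correct: this is a conflict between list and table.

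A reader might infer more than the text supports. That no examination precedes Visits 4 and 6 is wrong, because of the pre-discharge examination. That each of the 22 patients is cleared individually without data, or that a countable number would be re-infused before a cohort review, is not supported: section 16 speaks of aggregate review and no accrual rate is stated. That the organ-failure outcome would have no data is also unsupported, because the schedule table provides for the blood draws.

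**Conclusion.** The point holds as a mismatch of timing. Section 16 states one month as the review time and has the DSMB decide on the next infusion for the first 22 patients. The first post-discharge examination, CBC/CMP, DSA and MDS-UPDRS come 7.5-10.5 weeks after infusion 1 and 6.5-11.5 weeks after infusion 2, roughly 2 to 7 weeks after that review time. The DSA hold, which should catch sensitisation independently, names a week without a draw and lists no review of the Visit 4 or Visit 6 sample before the following infusion. The omission of CBC/CMP from the visit lists is a separate and lesser inconsistency.

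This rests on reading the one-month timing as applying to the decision to proceed, and on taking the visit windows at face value. The DSMB plan and the DSA algorithm figure could clarify intent. The change is worth making because it concerns the safety of repeat dosing and costs little; it does not show that the trial lacks safety monitoring.

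**What to change.** - **Section 16:** keep the one-month adverse-event review, but place the decision to proceed after Visit 4 (for infusion 2) and after Visit 6 (for infusion 3). For the first 22 patients, state that the DSMB sees those visits' CBC/CMP, DSA, examination and MDS-UPDRS with the aggregate data to date.
- **Section 11.2:** replace the references to weeks 8 and 21 with Visit 4 and Visit 6.
- **Section 10.1.4:** require each DSA result to be reviewed before the next infusion.
- **Sections 10.1.4 (Visits 4, 6, 8) and 10.1.5:** add blood CBC with differential and CMP, to match the schedule table.

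These are wording changes. They add no visit or draw beyond the table, and the 6.5 weeks or more before the next infusion leave room for results and a decision within the existing infusion windows. The cost is more frequent DSMB work, in small batches as patients pass Visits 4 and 6. Section 9 already expects the board to give an assessment within 24-48 hours of a severe event, so this looks workable.
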